## Abstract

**Background:**

Sweden is often held up as an example of a country with low child deprivation; yet, rates of relative deprivation are rising. Every municipality in Sweden is required to provide free, timely and accessible budget and debt counselling under the Social Services Act. The services have been encouraged to perform preventative practice with families; however, this has not been realised. The *Healthier Wealthier Families* (HWF) model embeds universal screening for economic hardship into child health services and creates a referral pathway to economic support services. Given the universal child health system in Sweden, which is freely available and has excellent coverage of the child population, implementation of the HWF model has potential to support families to access the freely available municipal budget and debt counselling and ultimately improve rates of child deprivation in Sweden.

**Methods/design:**

We will conduct a two-arm randomised waitlist-control superiority trial to examine the effectiveness and cost-effectiveness of the HWF model in the Sweden. A longitudinal follow-up with the cohort will explore whether any effects are maintained in the longer-term.

**Discussion:**

HWF is a collaborative and sustainable model that could maximise the effectiveness of current services to address child deprivation in Sweden. The study outlined in this protocol is the first effectiveness evaluation of the HWF model in Sweden and is a crucial step before HWF can be recommended for national implementation within the child health services.

**Trial registration:**

Clinicaltrials.gov; NCT05511961. Prospectively registered on 23 August 2022. https://clinicaltrials.gov/ct2/show/NCT05511961

## Strengths and limitations of this study

• This study will assess the effectiveness of the Healthier Wealthier Families (HWF) model on self-reported child deprivation in Sweden by randomised controlled trial• The study design includes measures on a number of hypothesised mediators, namely self-reported financial knowledge, financial control, readiness for change, parental mental health and financial stigma, which will give insight to the intervention logic model• Data on income, and sources of income, will allow the amount of financial gain that can be attributed to the HWF model to be described• Inclusion of personal goal attainment as an outcome will allow participants to express intervention expectations in their own words and report on how far these expectations have been met• The study design includes a cost-effectives evaluation that will consider group differences in capability-adjusted life-years• An internal pilot will assess the feasibility of the RCT processes• A 12-month follow-up will allow for exploration of whether any effects are maintained in the longer-term, albeit without the ability to make group comparisons at that stage

## Background

Sweden is often held up as an example of a country with low child deprivation; yet, rates of relative deprivation are rising. Since 2000, Sweden has witnessed a two-fold increase in the proportion of children living in relative poverty according to the European Union (EU) standard, i.e. living in a household with an income below 60 per cent of the national median [21]. The latest statistics place this figure at 17% [21]. When removing the aspect of relativity and considering families receiving social benefits and/or with a low-income standard, i.e. the household disposable income is lower than considered necessary for living expenses, the most recent figure stands at 9% [19]. Certain families are at greater risk than others. For instance, family constellation affects economic vulnerability, with increased risk of poverty [18] and elevated concerns regarding savings and managing unexpected costs [1] among single-parent households. Parental level of education and immigrant background have also been linked to higher risk of exposure to child poverty in Sweden ([1, 17]).

The impact of relative child poverty has been widely documented, with research reporting negative impacts across various outcomes including mental health problems, obesity, long-standing illness and mortality [10, 22]. The Family Stress Model [4] describes how parental psychological stress can mediate poor child outcomes; economic hardship affects parental mental health, causing parental conflict and/or difficulties with parenting, which in turn negatively affect child outcomes.

Budget and debt counselling, covering aspects such as budgeting, saving and debt management, can offer necessary support to families. Budget and debt counsellors work to improve financial knowledge and enable greater financial control. Not only has the ability to exert control over one’s finances been associated with financial wellbeing, it is actually a stronger predictor than income [23]. In some cases, the ability to meet costs can be improved even in the absence of being able to increase household income, through greater control over the existing income. Every municipality in Sweden is required to provide free, timely and accessible budget and debt counselling under the Social Services Act. The services have been encouraged to perform preventative practice with families; however, this has not been realised. Financial stigma could be playing a role in this. Research shows that Swedish people tend not to share their situation of economic vulnerability with governmental services, even though the services could improve their economic situation [6]. When parents share information about their economic situation, the moral dimension is something that is emphasised. Often, parents want to demonstrate they are financially responsible people, that they prioritise necessary costs and that they put the needs of their children first. Another important aspect to consider is readiness for change. Michie, Atkins, and West [12] describe that in order for behaviour change to take place, one must feel capable, have the opportunity to change, and be motivated to make the change.

Systematic integration of financial counselling and income maximisation services into routine health services can provide an opportunity for families to seek support and shift the focus away from the individual, instead emphasising need at the societal level. A recent systematic review identified examples targeting parents of young children across New Zealand, the UK and USA [3]. One such example is the *Healthier Wealthier Children* project, funded by the Scottish Government, which created information and referral pathways between the National Health Service (NHS) early years workforce and financial counselling services [16]. Pre-post evaluation of the model demonstrated monetary gain, as well as improved health, housing and quality of life [16]. The model has been integrated into the Scottish Government policy and adapted to international contexts, including Australia where it has been given the name *Healthier Wealthier Families* (HWF). Whilst the existing evidence is promising, more rigorous evaluation of the model is warranted to evaluate its effectiveness [3]. Given the universal child health system in Sweden, which is freely available and has excellent coverage of the child population [24], implementation of the HWF model has potential to support families to access the freely available municipal budget and debt counselling. This paper sets out the study protocol for a randomised controlled trial (RCT) evaluation of the HWF model in Sweden. The logic model for HWF in Sweden is illustrated in Fig. 1.

**Fig. 1 Fig1:**
[figure not shown]
Logic model for Healthier Wealthier Families in Sweden

### Objectives

The objectives of the trial are:To evaluate whether allocation to municipal budget and debt counselling services via the HWF model and provision of a financial guidance book (intervention arm) has an effect on self-reported child deprivation in comparison to similar families who only receive the financial guidance book (waitlist-control arm).To evaluate whether allocation to the intervention arm has an effect on self-reported financial knowledge, financial control, readiness for change, attainment of personal goals to improve one’s financial situation, parental mental health and financial stigma, which relate to the model theory of change.To describe the amount of financial gain, and sources of income, that can be attributed to the HWF model.To assess whether effects on self-reported child deprivation, financial control, financial knowledge, readiness for change, personal goals, parental mental health and financial stigma are maintained 12 months post-randomisation.To estimate the cost-effectiveness of the HWF model.

It is hypothesised that, when compared with the waitlist-control arm 3 months post-randomisation, families in the intervention arm will report a lower rate of child deprivation, measured as necessary items lacking on a standardised list, due to inability to cover costs. It is further hypothesised that, when compared with the waitlist-control arm, the intervention arm will report greater financial control and knowledge, and lower levels of mental health difficulties and financial stigma.

## Method

### Design

A two-arm randomised waitlist-control superiority trial (1:1 allocation ratio) will be conducted to evaluate the effectiveness of the HWF model in improving the financial situation of families who have self-reported economic difficulties. The intervention arm will be referred to budget and debt counselling immediately after randomisation and the waitlist-control arm 3 months later. Informed by Patient and Public Involvement (PPI), so all participants receive some form of support at randomisation, both arms will be offered a freely available financial guidance book. RCT assessments will take place at two points: pre-intervention (T1) and post-intervention (T2; 3 months after randomisation).

A longitudinal cohort study will be conducted with all participants, from both trial arms (intervention and waitlist-control). Longitudinal assessment will take place 12 months after randomisation (T3), to assess any changes in measures between T2 and T3. See Fig. 2 for the participant timeline.

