### Control arm

As described above, all participants receive a copy of the book. Those randomised to the waitlist control arm will be referred to the local financial counselling service after a period of 3 months.

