### Statistical methods

Baseline and demographic characteristics will be summarised using means and standard deviations (or medians and interquartile ranges) for continuous variables and percentages for categorical variables. For items that align with national survey questions, population-level comparisons will be made. Descriptive data will also be reported on process outcomes, e.g. number of families screened, proportion eligible for inclusion, and proportion consenting to participate.

The primary comparison of the trial arms will use an intention-to-treat framework. A regression analysis will be undertaken to quantify the extent to which a potential intervention effect on the primary outcome is determined by allocation to the intervention. Per-protocol comparison will be performed as a secondary analysis. Further moderation analyses will examine the associations between outcomes and participants’ characteristics. Differences in the means and proportions on measures between T2 and T3 will be assessed using parametric and non-parametric tests.

The cost-effectiveness analysis will compare the two arms of the trial at T2 follow-up using capability-adjusted life-years (CALY) gained as the outcome of interest. To analyse the cost differences between the two arms, we will collect information about intervention costs (i.e. personnel time, material, etc.) and societal resource use. We will express the final output as a cost/ CALY. Results will be presented as incremental cost-effectiveness ratios (ICER, expressing the cost per additional CALY gained). Uncertainty will be demonstrated using a cost-effectiveness acceptability curve, using bootstrapped regression estimates [5].

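### The 12-month analysis tests T2–T3 change with no split by arm, so it mixes maintenance in intervention families with the first response of waitlist families and does not identify whether effects last

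*Protocol article*

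**What the plan says.** The fourth aim under Objectives is to assess whether effects on child deprivation and six secondary measures "are maintained 12 months post-randomisation".

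Three places in the protocol article settle how this is to be done:

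- Design: "A longitudinal cohort study will be conducted with all participants, from both trial arms (intervention and waitlist-control"). The same paragraph makes change between T2 and T3 the thing to be assessed.
- Statistical methods: "Differences in the means and proportions on measures between T2 and T3 will be assessed using parametric and non-parametric tests". This is the only analysis named for T3, and arm is not mentioned.
- Strengths and limitations: the 12-month follow-up is described as exploration, "albeit without the ability to make group comparisons at that stage".

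On timing, Design says "The intervention arm will be referred to budget and debt counselling immediately after randomisation and the waitlist-control arm 3 months later", and Control arm repeats it: "Those randomised to the waitlist control arm will be referred to the local financial counselling service after a period of 3 months". Design labels the two RCT assessments "pre-intervention (T1) and post-intervention (T2; 3 months after randomisation").

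**The concern.** The label post-intervention for T2 is true of one arm only. For intervention families, T2 comes about three months after referral, so T2–T3 change shows whether an early effect holds or fades. For waitlist families, T2 falls at the point of referral, so T2–T3 change contains their first response to counselling.

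A T2–T3 difference taken over everyone averages these two quantities. The fourth objective could then be answered wrongly: improvement in newly referred waitlist families can look like further benefit, or can mask partial fading in intervention families. The stated limitation discloses that the between-arm comparison is lost. It does not disclose that the T2–T3 change means something different in each arm.

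**Working it through.** **Inputs from the protocol article.** 1:1 allocation and referral at month 0 or month 3 (Design); a 1-item effect, SD 3, significance level 0.05 and 71 families per group (Sample size).

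**Assumptions, not in the article.** Two-sided testing; SD 3 at both visits; T2–T3 correlation r = 0.5, with range 0.3 to 0.7; a waitlist gain of up to 1 item after referral; 71 families per arm with both visits. Sample size projects 50% loss without saying at which visit, so 36 per arm is also shown.

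**The plan's own figure.** No figure is given for the T2–T3 analysis. The stated 71 per group is for the T2 comparison. The usual formula gives 2 × (1.96 + 0.84)² × 3² / 1² ≈ 142 per group (284 in total), so 71 per group is not reproduced. That is a separate matter; 71 serves here only as an illustrative size.

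**Step 1: what the whole-cohort change measures.** Let fade be the rise in items lacked between T2 and T3 in the intervention arm, and gain the fall in the waitlist arm. With equal arms, and leaving aside any common time trend:

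pooled change = (fade − gain) / 2

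| Fade (intervention) | Gain (waitlist) | Pooled change |
|---|---|---|
| 0 (fully kept) | 0 | 0 |
| 0 (fully kept) | 1 | -0.50 |
| 0.5 (half lost) | 0.5 | 0 |
| 0.5 (half lost) | 1 | -0.25 |
| 1 (fully lost) | 0 | +0.50 |
| 1 (fully lost) | 1 | 0 |

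A pooled change of zero fits no loss, half loss or complete loss. A negative change fits full maintenance or half loss. This is non-identification, so it does not depend on sample size, SD or correlation.

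**Step 2: how often full maintenance would be read as further improvement.** Take fade 0 and gain 1.

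- SD of change within an arm = 3 × √(2(1 − r)) = 3.00 at r = 0.5.
- Each arm mean lies 0.5 from the pooled mean, which adds 0.25 to the variance: √(9 + 0.25) = 3.04.
- Standard error with 142 families = 3.04 / √142 = 0.255, and 0.5 / 0.255 = 1.96.
- Probability of significance is about 50% by normal approximation; 20,000 simulated trials with a paired t-test gave 49%.
- By the same approximation it is 38% at r = 0.3 and 71% at r = 0.7.
- With 36 per arm and r = 0.5: 0.5 / (3.04 / √72) = 1.40, or about 29%.

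**Step 3: what the intervention arm alone can show.** Its T2–T3 change is 0, +0.5 or +1 for effects fully kept, half lost or fully lost, whatever the waitlist arm does. Power to detect complete loss with 71 families is about 66%, 80% and 95% at r = 0.3, 0.5 and 0.7 (79% by simulation at 0.5). With 36 families and r = 0.5, 1 / (3 / √36) = 2.0, so power is about 52%. Power to detect half loss with 71 families is 22% to 44% over the same range of r.

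**The case against.** The strongest objection is that the article never says the arms will be pooled. Naming all participants from both arms may describe only who is followed up, and the tests could be run within each arm; an analysis plan that is not shown may say so. This stands in part, and a reader should not infer that pooling is a declared decision. But the article does more than stay silent. It defines one cohort, sets one contrast, gives an arm-free test and disclaims group comparison. Someone following that text would run a single-cohort test.

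A reader might also infer that the plan would typically hide complete loss of effect, because fade of 1 and gain of 1 cancel exactly. The documents do not support presenting this as the expected case. It needs the effect to have vanished 12 months after referral in one arm yet be intact about 9 months after referral in the other. If both had faded, the arm changes would be +1 and 0, and the pooled change of +0.5 would point to loss. Nor must the two changes have opposite signs: under full maintenance the intervention change is zero. Self-referral by waitlist families, which the Discussion treats as a real risk, would shrink the mixing by an unknown amount.

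Two further points stand. T3 lies outside the RCT assessments and is described as exploration. And the intervention-arm change is itself a before–after comparison that carries any time trend, so splitting by arm removes the mixing but does not supply a control.

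The remark that groups cannot be compared at T3 is fair if it means that no unreferred control remains. Read literally it is too strong, since the arms remain randomised to immediate versus delayed referral. But that contrast answers a question no objective asks, and omitting it is not an error.

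**Conclusion.** The point holds for the text as written. A T2–T3 change over all participants does not identify maintenance, so the named method cannot answer the fourth objective. This follows from the referral schedule and equal allocation alone.

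The size of the error is illustrative. With full maintenance and a 1-item waitlist gain, the cohort shifts by -0.5 items, and further improvement is declared in about 49% of trials at r = 0.5 and 71 per arm (roughly 38% to 71% for r from 0.3 to 0.7, and fewer with heavier loss). Partial fading can be masked in the same way; exact cancellation is an extreme case. These percentages rest on an assumed correlation, waitlist gain and T3 retention.

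The consequence is confined to the 12-month objective. The T2 primary comparison and the T2 cost-effectiveness comparison are unaffected.

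**What to change.** - In Design and Statistical methods, state that T2–T3 change is estimated separately by arm.
- Answer the fourth objective from the intervention arm's T2–T3 change with a confidence interval, and say that it is uncontrolled for time trend. A non-significant change should not be taken as proof of maintenance.
- Report the waitlist arm's T2–T3 change separately, as change after delayed referral.
- Use an arm-by-time model over T1, T2 and T3 where a T1 value exists. Goal attainment is rated only at T2 and T3, so analyse it on those two visits.
- In Strengths and limitations, replace the remark on group comparisons with a statement that no unreferred control remains at T3. The randomised T3 contrast, labelled as immediate versus 3-month-delayed referral, may be added as an optional supplement.

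**Cost.** Wording only, with no new data. The maintenance estimate uses about half the families, so its interval is about √2 ≈ 1.4 times wider. Its power to detect complete loss depends on the unknown correlation and T3 retention, and could be only about half if 36 families per arm remain.

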**Fig. 2 Fig2:**
[figure not shown]
Participant timeline with anticipated numbers

### Setting

The screening for the RCT will take place at children’s health care centres, known in Swedish as barnavårdscentraler (BVCs). BVCs examine the health of children (0–5 years) to monitor growth and development and provide advice and support to parents, e.g. about the child's development, breastfeeding, food and diseases. Parents are also offered vaccinations for their children at the BVC. Visits take place from just after birth until the child begins school. These services are offered free of charge and achieve excellent reach (99%) [24]. The RCT will focus on BVCs in municipalities experiencing high rates of children living in relative poverty. The 290 municipalities in Sweden have been categorised according to the proportion of children in households with income less than 60 percent of the median [20]. BVCs in the most severe categories (19.7–26.9%; and 27.0–46.0%) will be targeted for participation in the RCT. Concerning the larger municipalities, a more fine-grained categorisation will be conducted using local statistics, to be able to identify the proportion of children in households with income less than 60 percent of the median in residential areas.

### Participants

The target population is families with children in contact with BVCs. To be eligible for the project, the parent or caregiver needs to score on one or more items that indicate economic difficulties and not have been in contact with a financial advisory service in the last month. The screening questions were developed as part of an initial adaptation and pilot study, and include items used by the Swedish Inspection of Finance. The screening includes six items covering financial worry, ability to meet costs, occupation and handling unexpected costs and current use of financial advisory service(s):During the last 12 months, have you been worried that your family will run out of money at the end of the month?During the last 12 months, have you been able to pay current expenses such as rent, bills, insurance?During the last 12 months, have you had the opportunity to buy necessary items such as clothes and food for yourself and your children?Is there at least one person in your household who currently has a paid job?Would you be able to handle an unexpected expense of 20,000 SEK (approx. £1,500) without asking for help or borrowing money?Have you used a financial advisory service within the last month? *(By that we mean if you have had a scheduled meeting with a budget and debt counselor to get help with your economy)*

### Recruitment

During a routine BVC visit, the nurse will ask the parent/caregiver if they consent to answering questions about their economy. If they agree, the child health nurse will systematically work through an electronic screening form. The form has been co-designed with child health nurses, financial counsellors and families. It is hosted on a secure online platform called Research Electronic Data Capture (REDCap), which is specifically geared to support online and offline data capture for research studies and operations. It is fully customizable to meet the needs of this project and allows secure multi-site access with authentication and data logging that meet General Data Protection Regulation (GDPR) regulation requirements. It is a dynamic form that prompts the nurse to show informational material (e.g. a short video about the financial counselling service) at the appropriate moments during the screening discussion. The data are securely transferred to the research group. Basic data are captured for all families screened and personal details shared for those who consent to be contacted about study participation. A member of the research team then contacts the parent/caregiver to complete the informed consent procedure and the study questionnaire, which can be completed via REDCap, on paper, or orally. All parents/caregivers have the right to decline participation in the research study and can still gain access to the municipal budget and debt counselling service.

